## Abstract

**Background:**

Partial pancreatico-duodenectomy (PD) is the standard treatment for tumors of the pancreatic head. Today, preservation of the pylorus has been widely accepted as the surgical standard in this procedure. A common postoperative complication is the occurrence of delayed gastric emptying (DGE), which causes impairment of oral intake andpatients’ quality of life, prolongation of hospital stay and delay of further treatment (for example adjuvant chemotherapy). In a small number of two retrospective and one randomized studies, a modification by resection of the pylorus with preservation of the stomach has shown to reduce DGE incidence. The aim of the present study is to investigate the effect of pylorus resection on postoperative DGE in PD.

**Methods/Design:**

Patients undergoing elective PD for any indication equal or older than 18 years and who have given informed consent will be included. Patients will be randomized to either PD with pylorus preservation or PD with pylorus resection and complete stomach preservation. Sample size (n = 89 patients per group) is calculated on an assumed difference in DGE incidence of 20%. Primary study endpoint is DGE within 30 days; secondary endpoints are operation time, blood loss, morbidity, mortality, hospital stay and quality of life (QoL).

**Discussion:**

DGE is a relevant clinical problem following PD with a great impact on patients’ recovery, length of hospital stay, QoL and consecutive adjuvant therapies. As there is no causal therapy, prevention of DGE is essential to improve outcome. The technical modification of pylorus resection may offer a simple and effective method for this purpose. The present study is designed to increase the existing body of evidence and potentially change the future standard surgical procedure of PD.

**Trial registration:**

German Clinical Trials Register DRKS00004191.

## Background

Partial pancreatico-duodenectomy (PD) is the standard treatment for tumors of the pancreatic head as well as benign precursor lesions such as intraductal mucinous neoplasia (IPMN) that require a resective surgical approach
[1,2]. Classical partial pancreatico-duodenectomy with resection of the distal stomach as the historical standard procedure was modified in the 1970s by Traverso, who introduced preservation of the pylorus
[3]. This modification (ppPD) has been widely accepted to be equally effective compared to the classical pancreatico-duodenectomy with regard to tumor recurrence and long-term survival in numerous studies
[4]. A well-known complication after either method of PD is the occurrence of delayed gastric emptying (DGE)
[5,6]. DGE causes impairment of oral intake and patients’ quality of life (QoL), prolongation of hospital stay and delay of further relevant treatments (for example start of adjuvant chemotherapy). This complication is regarded as a functional impairment of the physiological propulsive regulation of the stomach and especially the pylorus. In recent trials, it has been shown that antecolic reconstruction is superior to retrocolic duodeno-jejunostomy in terms of the incidence of DGE
[5,6]. In 2007, the International Study Group of Pancreatic Surgery (ISGPS) proposed a standardized definition of DGE with three grades of severity (A-C)
[7]. The grading system included the use of a gastric tube, time to solid oral food intake, symptoms like distension and vomiting as well as the use of prokinetic medication. This definition was evaluated in the patient collective in Heidelberg
[8]. The overall frequency of DGE within this collective was 45%, including 28% DGE grade A, 8% grade B and 9% grade C.

In a recent study published in 2010 by Kurahara *et al*.
[9], the frequency of DGE using the ISGPS definition was examined in a retrospective data analysis comparing 48 patients that underwent ppPD vs. 64 patients in which the pylorus was resected (prPD). Resection was limited to the pyloric ring with preservation of the entire stomach. Reconstruction was then performed as a gastro-jejunostomy in the distal antrum of the stomach. In this study, DGE frequency was 34.8% after pylorus preservation vs. 13.0% when the pylorus was resected. This is in line with a retrospective study published in 2000
[10] comparing similar approached in 39 (ppPD) vs. 33 (prPD) patients. DGE frequency was 33% vs. 12% confirming an approximate difference of 20%. A current Japanese publication by Kawai *et al*.
[11] has focused on the issue of pylorus resection in a randomized controlled study. The authors have included 64 patients with ppPD vs. 66 patients that underwent prPD with the endpoint DGE between 7 days and 6 months postoperatively. The observed frequency of DGE was 17.2% and 4.5% respectively (*P* = 0.02). Although this study showed a clear trend toward the results observed in the former retrospective studies, several shortcomings (only one randomized controlled trial (RCT), other studies performed retrospectively, overall small number of patients) do not allow drawing a final conclusion and the surgical consequences. From the mentioned studies, it seems reasonable that resection of the pylorus may offer significant benefits in the postoperative phase regarding the frequency of DGE and consecutive quality of life and may be superior to the standard ppPD. Yet, scientific evidence to support this hypothesis is rather weak.

Therefore, the aim of the present study is to investigate the two modifications of PD (ppPD vs. prPD) in a randomized controlled setting to confirm or contradict the hypothesis and show potential shortcomings of both methods, which are not yet obvious. The results can add more evidence to the current discussion and have a potential impact on a widely performed standard operation in pancreatic surgery.

## Methods

### Study population

The study population consists of all patients scheduled for PD for any indication. Further inclusion criteria are age equal or older than 18 years and having given informed consent. Participation in another intervention trial with interference of intervention and/or outcome of this study and expected lack of compliance as well as language problems represent the only exclusion criteria. The study protocol has been approved by the local ethics committee (University of Heidelberg S-121/2012).

### Randomization and surgical procedures

Patients are intraoperatively randomized to either of the two groups after the surgeon has confirmed that preservation of the pylorus is technically and oncologically possible. Randomization is performed as an unstratified block randomization with fixed block sizes in a 1:1 allocation ratio using established randomization software. Block size is kept confidential until completion of recruitment. Standard PD with preservation of the pylorus is performed by dividing the duodenum 2 cm distal of the pylorus with a linear stapling device under preservation of the gastric vessels along the lesser and the greater curvature. Antecolic duodeno-jejunostomy is performed at the end of the operation approximately 50 cm distal to the hepato-jejunostomy by an end-to-side anastomosis using two-layer monofilament atraumatic running sutures. Resection of the pylorus is performed with preservation of the stomach by the use of a linear stapling device with complete preservation of the gastric vessels along both curvatures to preserve perfusion of the distal stomach via the gastroepiploic arcade and the left gastric artery, respectively. Antecolic gastro-enterostomy is performed by an end-to-side gastro-jejunostomy using a two-layer running monofilament atraumatic suture technique as well. In both groups, nasogastric tubes are removed as soon as mechanical ventilation is stopped, usually at the end of the operation. Follow-up examinations are scheduled at day 7, 14 and 30 postoperatively. The study protocol is shown in Figure 
1.

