### Methods against bias

#### Selection bias

Consecutively screened and eligible patients will be included after initiation of the study. In order to achieve comparable intervention groups, patients will be allocated concealed by intraoperative randomization at the day of surgery using a centralized web-based tool (
http:// randomizer.at). Block randomization will be performed to achieve totally equal group sizes. A sufficient number of patients will be recruited according to the sample size calculation in order to prevent random error and to achieve sufficient power for hypothesis testing of the primary endpoint.

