#### Information bias

All surgeons who participate in this trial will be instructed which treatment procedures are applicable in both groups. Blinding of surgeons is not feasible due to the nature of the interventions. However, patient and observer documenting the endpoints during the postoperative visits will be blinded.

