### Sample size calculation

Sample size calculation is based on the primary endpoint ‘frequency of DGE 30 days after surgery’. On the basis of previous literature mentioned in the background section, an assumed absolute risk of 20% difference in DGE frequency is the basis for the calculation assuming 32% DGE in group 1 (ppPD) and 12% in group 2 (prPD).This leads to a calculated number of 89 patients who have to be treated in each group assuring a power of 90% at a two-sided level of significance of 5%. As the individual results for the primary endpoint are available within 30 days after surgery, the expected drop-out rate is small. Nevertheless, a potential dilution of the treatment effect due to drop-outs is taken into account; it is assumed that this can be compensated by additional 10% of patients to be randomized, and therefore the total sample size required amounts to n = 198 patients.

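### Fixed block sizes, with unblinded surgeons judging suitability just before randomisation, leave a material share of allocations potentially predictable

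*Protocol article*

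**What the plan says.** The Protocol article, under Randomization and surgical procedures, fixes the scheme: "Randomization is performed as an unstratified block randomization with fixed block sizes in a 1:1 allocation ratio". The same section adds that "Block size is kept confidential until completion of recruitment". Patients enter randomisation "after the surgeon has confirmed that preservation of the pylorus is technically and oncologically possible".

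Under Selection bias, it says that "patients will be allocated concealed by intraoperative randomization at the day of surgery using a centralized web-based tool", and gives the purpose of blocking: "Block randomization will be performed to achieve totally equal group sizes". Under Information bias, it says that "Blinding of surgeons is not feasible due to the nature of the interventions", although "patient and observer documenting the endpoints during the postoperative visits will be blinded". Under Confounding, it relies on randomisation to control potential confounding.

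The block length and the number of operating surgeons are not given. The Sample size calculation section sets 198 patients in total. Under Trial status, recruitment is open and the first patient was enrolled in January 2013.

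**The concern.** Permuted blocks force balance at the end of every block, so late allocations in a block depend on the earlier ones. With a constant, short length and one unstratified list there is a single sequence to follow, and a person who knows its history can sometimes know the next arm.

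That matters most where the same person controls entry. Here the surgeon judges technical and oncological suitability for pylorus preservation immediately before allocation. The article gives no objective criterion for that judgement, and the surgeon cannot be blinded to the allocations of the patients on whom he or she operates. A borderline patient could be entered or declared unsuitable with the likely arm in mind. The arms would then differ at baseline. Blinded patients and observers guard against biased measurement of the endpoint, not against selection at entry.

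**Working it through.** **The plan's own figure.** Inputs from the Sample size calculation section: 32% and 12% DGE, two-sided 5%, power 90%. With pooled variance under the null (mean rate 22%), n per arm = [1.96·√(2·0.22·0.78) + 1.2816·√(0.32·0.68 + 0.12·0.88)]² / 0.20² = (1.148 + 0.729)² / 0.04 ≈ 88.1, so 89. With drop-out, 178 / 0.9 = 197.8, so 198. The sample size reproduces and is not at issue.

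**Allocations determined in advance.** Assumptions: one constant block size 2m, known to the guesser, and all earlier allocations seen. The expected share of allocations forced by earlier ones is 1/(m+1). The share guessed correctly comes from always naming the arm under-represented in the current block (chance is 50%).

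| Block size | Fully determined | Of 198 | Correct guesses |
|---|---|---|---|
| 2 | 50% | 99 | 75.0% |
| 4 | 33% | 66 | 70.8% |
| 6 | 25% | about 50 | 68.3% |
| 8 | 20% | about 40 | 66.6% |
| 18 | 10% | about 20 | 62.2% |
| 22 | 8% | about 17 | 61.2% |

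**Does confidentiality of the size close the gap?** The running imbalance can never exceed half a block, so a short block eventually shows its length. A block reaches its maximum imbalance with probability 2/C(2m, m). For size 4 this is 2/6 = 1/3. For size 6 it is 2/20 = 1/10, or about 3 of the 33 blocks in 198 patients. For size 8 it is 2/70, about 3%. Naming the under-represented arm also needs only the running tally, not the block size. Confidentiality is therefore weak protection for short blocks and good protection for long ones.

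**How much depends on visibility?** The tally rule was simulated over 198 patients for a surgeon who sees only a random part of the sequence and counts only those cases. For blocks of 4 and 6, accuracy was about 71% and 68% with everything seen, 52% and 53% with half seen, and about 52% for both with a quarter seen.

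**Effect of random block sizes.** This was simulated with a guesser who knows the set of sizes, sees every allocation and updates probabilities optimally. With sizes 4, 6 and 8, about 2% of allocations are known with certainty and best-guess accuracy is about 68%. With sizes 4 and 6, the figures are about 5% and 69%.

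**Illustration of consequence.** Assume, without support from the document, that 25% of allocations are foreknown, that all are exploited, and that this shifts those patients' DGE risk up by 5 points in one arm and down by 5 in the other. The arms then differ by 0.25·5 + 0.25·5 = 2.5 points; a shift of 10 gives 5 points. Exact enumeration of the two-sided pooled test at 99 per arm, with the difference centred on the base rate and no true treatment effect, gives:

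| Base rate | No imbalance | 2.5 points | 5 points |
|---|---|---|---|
| 32% (plan's ppPD rate) | 5.1% | 6.7% | 11.8% |
| 22% (mean of the two planned rates) | 5.2% | 7.3% | 13.9% |

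**The case against.** The strongest reply is that the article describes real safeguards. Allocation is central and web-based, made during surgery, with consecutive screening and an undisclosed block size. Fixed blocks behind such a system are a recognised choice, and nothing shows that any surgeon tracked the sequence. This stands as far as size is concerned: the determined share runs from 50% to under 10% with the block length, and the advantage nearly disappears when half the sequence is unseen. It does not remove the weakness, because a web tool hides the list but not what can be inferred from earlier allocations.

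A second reply is that random block sizes scarcely change best-guess accuracy: about 68%, against 68% to 71% for fixed blocks of 6 or 4. That is correct. The gain lies in removing certain predictions.

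Three stronger readings are tempting but not supported:
- A reader might infer that surgeons see every allocation. The article says only that they cannot be blinded. It does not say how many there are or whether they share the sequence.
- A reader might infer from 198 patients and exactly equal groups that the block size is 2 or 6, the short even divisors of 198. That assumes one constant size and a stop at exactly 198. The article uses the plural for block sizes, states equality as an aim, and reaches 198 by a drop-out allowance.
- A reader might take the type I error figures as an estimate of bias in this trial. They rest on invented risk shifts and full exploitation in one direction.

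**Conclusion.** The point holds as a conditional risk. The scheme, the unblinded surgeons and the judgement immediately before randomisation are all stated in the article, so this is a design choice made there and not a detail left to another document. If the block is short, its size has been inferred and the full sequence is known, a quarter to a third of allocations (about 50 to 66 of 198, for blocks of 6 or 4) could be known beforehand. With longer blocks the share is smaller, and with half the sequence unseen the tally rule does little better than chance. The existing safeguards reduce the risk but do not close it. The article does not show that allocations were predicted or that the arms are imbalanced. The point is a worthwhile, inexpensive improvement, not a fatal flaw.

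**What to change.** Generate the remaining list in the same web tool with randomly varying block sizes, and disclose neither the sizes nor the set from which they are drawn until recruitment ends. Under Randomization and surgical procedures, replace the reference to fixed blocks accordingly. Under Selection bias, change the aim of exactly equal groups to approximately equal groups.

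The cost is a new list and two edited sentences. Final group sizes may differ by up to half a block. With a largest block of 8 that is 4 patients, for example 101 to 97. At the planned rates, power by the normal approximation is then 93.0%, against 93.1% at 99 per arm. If the present list is left in mid-block, up to half of that block is added to the possible difference.

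Two limits should be recorded with the change: it protects only patients not yet randomised, and someone who sees the whole sequence can still guess better than chance.

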**Figure 1 F1:**
[figure not shown]
Flow chart of the PROPP study.

### Study objectives

Primary efficacy endpoint is the frequency of postoperative DGE according to the international ISGPS definition (Table 
1) 30 days after index operation, compared between the two intervention groups
[7]. Key secondary endpoints are operation time (skin cut to last knot), blood loss (ml), overall morbidity according to the Clavien-Dindo classification
[12], 30-day mortality, postoperative hospital stay and QoL on postoperative day 30.

**Table 1 T1:** **DGE (grading A-C) according to the ISGPS definition**[7]

**Grade**	**Nasogastric tube**	**Solid food intake**	**Vomiting distension**	**Prokinetic medication**
**A**	4-7d/reinsertion > d3	d7	±	±
**B**	8-14d/reinsertion > d7	d14	+	+
**C**	>14d/reinsertion > d14	d21	+	+

DGE, delayed gastric emptying; ISGPS, International Study Group for Pancreatic Surgery.

### Methods against bias

#### Selection bias

Consecutively screened and eligible patients will be included after initiation of the study. In order to achieve comparable intervention groups, patients will be allocated concealed by intraoperative randomization at the day of surgery using a centralized web-based tool (
http:// randomizer.at). Block randomization will be performed to achieve totally equal group sizes. A sufficient number of patients will be recruited according to the sample size calculation in order to prevent random error and to achieve sufficient power for hypothesis testing of the primary endpoint.

#### Information bias

All surgeons who participate in this trial will be instructed which treatment procedures are applicable in both groups. Blinding of surgeons is not feasible due to the nature of the interventions. However, patient and observer documenting the endpoints during the postoperative visits will be blinded.

#### Confounding

Potential confounding will be controlled due to randomization.

Performance bias will be minimized by applying a standardized treatment manual for the surgical as well as the perioperative procedures. Thus, all surgical procedures will be defined in operation manuals. Moreover, medical treatment including prokinetic drugs, proton pump inhibition, antibiotics and octreotide analogs will be defined *a priori*. Routine management of nasogastric tubes and endoscopic examination in case of DGE will be defined as well. Blinded assessment of the primary endpoint 30 days after the surgical procedure will be performed by independent observers (not aware of the respective surgical procedure) to minimize measurement bias. Patients will be kept blind to the randomized and performed procedure. Unblinding of the patients will be possible in situations requiring reinterventions.

### Sample size calculation

Sample size calculation is based on the primary endpoint ‘frequency of DGE 30 days after surgery’. On the basis of previous literature mentioned in the background section, an assumed absolute risk of 20% difference in DGE frequency is the basis for the calculation assuming 32% DGE in group 1 (ppPD) and 12% in group 2 (prPD).This leads to a calculated number of 89 patients who have to be treated in each group assuring a power of 90% at a two-sided level of significance of 5%. As the individual results for the primary endpoint are available within 30 days after surgery, the expected drop-out rate is small. Nevertheless, a potential dilution of the treatment effect due to drop-outs is taken into account; it is assumed that this can be compensated by additional 10% of patients to be randomized, and therefore the total sample size required amounts to n = 198 patients.

### Documentation and data handling

All protocol-required information collected during the trial is entered in the case report form (CRF). The completed CRFs are reviewed and signed by the investigator or by a designated sub-investigator and sent to the Institute for Medical Biometrics and Informatics (IMBI) for data entry. The data will be managed and analyzed in the joint unit of the clinical study center and IMBI in accordance with the appropriate standard operating procedures (SOPs) valid in the IMBI. A safety analysis will be based on the set of all patients for which one of the interventions was applied. Serious adverse events will be tabulated, absolute and relative frequency, severity and the relationship to the intervention will be given and compared between the intervention groups.

## Discussion

DGE is a common complication after PD reported in numerous studies, initially under the use of various definitions
[5,6]. Consequently, highly differing rates of DGE were reported, which led to the introduction of the standardized definition of the ISGPS in 2007
[7]. The proposed definition has been evaluated clinically in large patient groups after ppPD and surprisingly shown an actual overall DGE incidence of up to 45%
[8].

DGE represents a therapeutically difficult complication that prolongs patients’ hospital stay and postpones or even inhibits the start of adjuvant chemotherapy in tumor patients. Therefore, the need to reduce the frequency of DGE is obvious. In two retrospective studies a 20% reduction of DGE after prPD was shown
[9,10]. A current randomized trial
[11] confirmed a reduction of DGE although the 13.7% difference between prPD and ppPD in this study was less pronounced. As the number of patients in these available studies is limited and the study designs are heterogenous, evidence is still weak and further studies are necessary to evaluate the actual impact of prPD on DGE.

It remains unclear if pylorus resection influences the severity of DGE in terms of the ISGPS grading A-C. Furthermore, no standardized therapy of DGE is defined yet, which impairs the significance of the respective results. Reconstruction technique with stenting of the pancreatic duct in the RCT
[11] cannot be considered as the standard reconstruction. As the overall fistula rate was rather high in this study, this could have a substantial influence on DGE. Postoperative nasogastric tube management is not standardized. From our experience, tube removal can be routinely done at the end of the general anesthesia and may also influence stomach motility in the further course.

DGE is regarded as a functional impairment of gastric motility and normal pyloric function, which has been supported by the observation that antecolic reconstruction of the duodeno-jejunal passage significantly lowered its incidence, probably due to the advantage of less chemical irritation by potential subclinical leakage of the pancreatic anastomosis within the first postoperative days. An additional anatomical modification by removing the pylorus could significantly enhance this effect. Of course, resection of the pylorus implies the risk of reflux symptoms in the long-term follow-up. Yet, this has not been proven and any long-term problems, for example gastric stump cancer after 10 to 15 years can be disregarded in pancreatic cancer patients. In patients undergoing PD for benign pathologies, however, these problems have to be taken into account and should be evaluated in long-term studies. A differential surgical approach for malignant and benign indications may be considered in case of clinically observed reflux-associated symptoms. Regarding perioperative morbidity and mortality, the available studies on prPD show comparable results underlining the feasibility of pylorus resection
[9-11].

In conclusion, there is increasing evidence that prPD may be associated with a decreased rate of DGE. The present study as a large randomized trial based on the currently available literature is planned to confirm these findings, which may alter surgical procedures in PD.

